## Abstract

**Background:**

Education and health are crucial topics for public policies as both largely determine the future wellbeing of the society. Currently, several studies recognize that physical activity (PA) benefits brain health in children. However, most of these studies have not been carried out in developing countries or lack the transference into the education field. The Cogni-Action Project is divided into two stages, a cross-sectional study and a crossover-randomized trial. The aim of the first part is to establish the associations of PA, sedentarism, and physical fitness with brain structure and function, cognitive performance and academic achievement in Chilean schoolchildren (10–13 years-old). The aim of the second part is to determinate the acute effects of three PA protocols on neuroelectric indices during a working memory and a reading task.

**Methods:**

PA and sedentarism will be self-reported and objectively-assessed with accelerometers in a representative subsample, whilst physical fitness will be evaluated through the ALPHA fitness test battery. Brain structure and function will be assessed by magnetic resonance imaging (MRI) in a randomized subsample. Cognitive performance will be assessed through the NeuroCognitive Performance Test, and academic achievement by school grades. In the second part 32 adolescents (12–13 year-old) will be cross-over randomized to these condition (i) “Moderate-Intensity Continuous Training” (MICT), (ii) “Cooperative High-Intensity Interval Training” (C-HIIT), and (iii) Sedentary condition. Neuroelectric indices will be measures by electroencephalogram (EEG) and eye-tracking, working memory by n-back task and reading comprehension by a reading task.

**Discussion:**

The main strength of this project is that, to our knowledge, this is the first study analysing the potential association of PA, sedentarism, and physical fitness on brain structure and function, cognitive performance, and academic achievement in a developing country, which presents an important sociocultural gap. For this purpose, this project will use advanced technologies in neuroimaging (MRI), electrophysiology (EEG), and eye-tracking, as well as objective and quality measurements of several physical and cognitive health outcomes.

**Trial registration:**

ClinicalTrials.gov identifier: NCT03894241 Date of register: March 28, 2019. Retrospectively Registered.

**Electronic supplementary material:**

The online version of this article (10.1186/s12887-019-1639-8) contains supplementary material, which is available to authorized users.

## Background

Evidence shows a positive influence of physical activity (PA) on brain structure and function, cognition and academic achievement throughout the lifespan [1–5]. At present, international guidelines recommend at least 60 min/day of moderate-to-vigorous physical activity (MVPA) in children older than 5 years, based on its health benefits [5–7]. However, industrialized societies are characterized by high levels of physical inactivity, sedentariness and obesity among children and adolescents [8]. This panorama increases the likelihood of suffering from chronic diseases, dementia and ill-being later in life, facts that are considered of global political concern [9–12].

In this context, schools play a fundamental role because children spend most of their day in these educational establishments. From all of the school subjects, physical education (PE) is the most suited with the potential to increase PA levels of schoolchildren as well as to raise awareness of the need of having a physically active lifestyle. Further, several studies have reported that PE did not impair academic achievement [13]. In fact, increasing both duration and intensity of PE in schools may even enhance both cognition and academic achievement (e.g., mathematics or language skills) [14, 15]. Despite those findings, many schools have decided to maximise the time spent on instrumental school subjects, such as maths or native languages, therefore decreasing PA levels in schools as students pass their course. This strategy could not only be ineffective but also detrimental for academic levels as literature suggests that fitter children hold better brain structure and function [16–19]. Beyond the cognitive improvements, there is no doubt that PA is related to children’s well-being and health [20–22]. Therefore, both health and educational complications could be exacerbated by the limited time of school-based MVPA [23].

In the particular case of Chile, self-reported PA in children has been favourably related to academic achievement [24–26], but studies using objective measures of PA are scarce and inconsistent, even worldwide [4, 27]. Besides PA, both cardiorespiratory and muscular fitness have also been associated with better academic achievement in mathematics and language measured through a national standardized test, the “System for Assessment of Educational Quality” (SIMCE in Spanish) [28]. Likewise, an obese status, excessive screen time, and low nutritional quality have been associated with worse school grades [3, 29–31]. This shows the multifactorial nature of improving cognitive and academic achievement through PA in children.

Mainly physiological mechanism have been used to explain the positive associations of PA level and physical fitness with cognitive function and academic achievement [32]. However, other variables related to educational context, such as the characteristics of PE lessons, the psychological school stress, the sleep quality or the health-related quality of life, have been studied less respect to effect on brain health, and especially in developing countries.

With the aforementioned, it seems necessary and justifiable to carry out a study that tries to cover both health and educational aspects in order to explain the benefits of PA on brain, cognitive and academic performance. This is particularly important in the sociocultural context of Chile due to several key aspects in youth: i) approximately 35% suffer from overweight/obesity [33]; ii) the level of physical inactivity reaches around 70% [23, 34]; iii) there is a high proportion of insufficient academic levels and of students that do not reach minimum learning skills [35], and; iv) high socioeconomic status segregation and market dynamics characterize the national education system [36].

Regarding the last point, the Chilean’s education system is harshly criticized due to the privatization of schools, the voucher system based on average attendance, the creation of incentives and penalties for schools and teachers [37]. These characteristics increase the inequality among students, which initially is originated by a well-known socioeconomic status gap. Indeed, the Chilean educational system estimates the school vulnerability index (SVI), which is an indicator of the degree of educational establishment vulnerability (ranging from 0 to 100, indicating what percentage of students presents in an unfavourable socioeconomic status and therefore, they become priority for the government policies) [38]. Despite the above the Chilean education system is one of the highest-performing in Latin-America but it also presents one of the highest within-country variability in outcomes [39]. In this line, there is a strong relationship between student achievement, socioeconomic status, and financing system of schools [40].

In other context, most of evidence trying to explain the underling mechanisms by which PA improves cognitive and brain functioning have been performed in developed countries [17, 41, 42] and in a well-controlled laboratory settings [43–45]. But, it is also important to develop cross-sectional studies in a more unfavourable sociocultural context as well as experimental studies in a more realistic environment to ensure the integration into the education field.

Experimental trials recently published show that cognitive-related brain activity (e.g., EEG [electroencephalography] oscillations and event-related potentials) is acutely modified after a single bout of PA, boosting cognitive performance in adults [43–46] and children [45]. Whereas there are several mechanisms by which an acute bout of PA can improve brain functioning or cognitive performance, various issues remain unclear [47]. In fact, to date there is not consensus about dose, intensity, duration and type of the PA that better improves brain and cognitive performance, or how long does this effect persists after a single bout of PA [48].

As academic achievement could improve after a single session of PA through a positive effect over working memory and reading [27, 49, 50], it seems to be interesting to study diverse protocols of exercise which can be included within the PE lesson. Despite this idea, with the current quality and quantity of scientific evidence in this field, it is still difficult to visualize a clear direction to establish future recommendations in the school context to improve brain structure and function, cognitive performance and academic achievement through PA.

The purpose of this manuscript is to describe the rationale, design and methods of the “Cogni-Action Project”, which will explore (i) the relationship between PA, sedentarism, physical fitness, brain structure and function, cognitive performance and academic achievement, and (ii) the acute effects of three PA protocols (interval and continuous exercise) and sedentary control condition on neuroelectric activity during resting state and during a working memory and reading task in a large sample of Chilean youth. In addition, this project will investigate the association with other relevant variables related to school context.

## Method and design

### Design and participants

The Cogni-Action Project presents a two-fold design with a cross-sectional investigation and a crossover-randomized trial (ClinicalTrials.gov identifier: NCT03894241). This project has been approved by the Ethics Committee of *Pontificia Universidad Católica de Valparaíso* (BIOEPUCV-H103–2016). In all aspects, this research will be conducted according to the Declaration of Helsinki. Written consent will be obtained prior to participation from the school principal and parents, as well as assent of participants. Any protocol modifications will be communicated and registered on ClinicalTrials.gov.

Children and adolescents from 5th to 8th grades (10–13 years old) are recruited from public and private schools in Valparaiso, Chile. This age-group has been selected because of its limited scope, scope, which (tries to) avoid possible methodological bias due to the critical period where preadolescent and adolescent transit through the development of different personal characteristics [51]. It is also an interesting stage of life related to changes in health-related lifestyles, which could have a long-term impact [52], especially in cognition and brain development [53]. A graphical description of the study design, sample and measurements is presented in Fig. 1.

**Fig. 1 Fig1:**
[figure not shown]
Cross-sectional and cross-over RCT study design

During the first part (i.e., cross-sectional study), measurements will take place in public and private schools, with two visits of 4 h each separated by 8 days. At the first visit, questionnaires, cognitive performance and anthropometric measurements will be assessed, followed by accelerometers placement. During the second visit, physical fitness and other questionnaires will be evaluated, plus accelerometer removal. A detailed description of all evaluations can be found in the measurements section.

Regarding the second part (i.e., crossover-randomized trial), children will be randomized to each protocol session, participating in all of them with two-weeks apart. Thus, they will assist to our gym to perform one of the three protocol and subsequently they will be move to a laboratory where they will undergo EEG and eye-tracking measurements during resting state condition and during two different cognitive tasks. More details can be found in following sections.

### Recruitment and randomization

An open invitation to schools from Valparaiso will be extended after consulting the database of the Chilean Ministry of Education, available at *www.mime.mineduc.cl/mvc/mime/portada*. Then, we will meet with principals to inform about the whole project. After accepting to participate, children, adolescents, and theirs parents will be invited to a new meeting where a full description of the scientific background, objectives, and safety will be given by our research group. During this session, parents and children must sign their participation consent.

### Inclusion/exclusion criteria on total sample

#### Cross-sectional study

##### Total sample

Inclusion/exclusion criteria will be, girls and boys from 5th to 8th grades (10–13 years old) will be included. For ethical reasons, children who present any physical, psychiatric and/or psychological disability will also be included in the cross-sectional study if both children and parents approve their participation. Once the evaluation process is finished, these children could be excluded from the main analysis.

##### Total sample size and power

Power calculation was based on the total enrolment of children and adolescents (5th to 8th grades) indicated by the Chilean Ministry of Education (universe *n* = 951,962) in the year 2016, and assuming an alpha error of 5%, confidence interval of 99, 50% of heterogeneity, and with a 20% dropout. Hence, a total of 797 participants are adequate sample for the cross-sectional part of the project.

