##### Subsample size and power

From those 797 children, for the calculation of the ACC subsample, we assume an alpha error of 5%, a confidence interval of 99, 50% of heterogeneity, and a 20% dropout, resulting in 436 participants. For the MRI subsample calculation an error of 10% was assumed, with a confidence interval of 90, 50% of heterogeneity, and with a 20% dropout, resulting in 76 participants.

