##### Total sample size and power

For feasibility reasons, the school chosen for the development of exercise sessions is close to our laboratory. Sample size is estimated according to the mean difference of two independent samples from a randomized controlled trial were a working memory task (2-back) was tested [56]. Children control group achieved a positive variation (∆ = 2.05 ms; SD = 93.1) while exercise group a negative variation (∆ = − 69.45 ms; SD = 91.6) [56]. A loss rate of 20% was considered. Statistical power analysis indicated that at least 32 participants would yield adequate power (i.e., > 80%) and α (i.e., < 0.05), with a detectable variation of 71.50 ms (∆ between experimental conditions – control condition).

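### The three precision-based sample sizes (797, 436 and 76) allow for a 16.7% loss, not the stated 20%

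*Protocol article*

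**What the plan says.** In the cross-sectional section Total sample size and power, the protocol article starts from a school population of 951,962 and calculates the total "assuming an alpha error of 5%, confidence interval of 99, 50% of heterogeneity, and with a 20% dropout". It concludes: "Hence, a total of 797 participants are adequate sample for the cross-sectional part of the project".

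In the section Subsample size and power, the total becomes the population for the next step ("From those 797 children, for the calculation of the ACC subsample"). For accelerometry the article says "we assume an alpha error of 5%, a confidence interval of 99, 50% of heterogeneity, and a 20% dropout, resulting in 436 participants". For MRI, "an error of 10% was assumed, with a confidence interval of 90, 50% of heterogeneity, and with a 20% dropout, resulting in 76 participants".

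The article does not say how the 20% was applied in any of these calculations.

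**The concern.** A dropout rate is a proportion of the children enrolled. To have n children left after losing 20%, a study must enrol n/0.8, which is 25% more than n. Adding 20% to n is a common slip and leaves 0.96n after the loss. If the stated totals were built that way, they miss the plan's own precision target under the plan's own dropout assumption, and the text claims a protection that the numbers do not give. The total also serves as the population for both subsamples, so a correction to it carries forward.

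**Working it through.** **Inputs**, all from the two cross-sectional sample-size sections:
- Total: N = 951,962, error 5%, confidence 99% (z = 2.576), p = 0.50, dropout 20%.
- Accelerometry: N = 797, otherwise the same.
- MRI: N = 797, error 10%, confidence 90% (z = 1.645), p = 0.50, dropout 20%.

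The 5% is labelled an alpha error, but a separate confidence level is given beside it, and the stated totals reproduce only if it is used as the margin of error e. I use it so.

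**Step 1: required number before dropout.** n0 = z²p(1 − p)/e², then the finite-population correction n = n0/(1 + (n0 − 1)/N).
- Total: n0 = 663.49; n = 663.03, rounded up to 664.
- Accelerometry: n = 663.49/(1 + 662.49/797) = 362.3, rounded up to 363.
- MRI: n0 = 67.64; n = 67.64/(1 + 66.64/797) = 62.4, rounded up to 63.

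**Step 2: which inflation reproduces the stated figures?**

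| Sample | Required n | n × 1.2 | n / 0.8 | Stated |
|---|---|---|---|---|
| Total | 664 | 796.8 → 797 | 830 | 797 |
| Accelerometry | 363 | 435.6 → 436 | 453.75 → 454 | 436 |
| MRI | 63 | 75.6 → 76 | 78.75 → 79 | 76 |

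One rule (round up, multiply by 1.2, round up) reproduces all three exactly. Division by 0.8 misses by 33, 18 and 3. Rounding of z does not close the gap: with z between 2.57 and 2.58 the total divided by 0.8 stays between 826 and 833, and with z between 1.64 and 1.65 the MRI figure stays at 79.

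**Step 3: loss actually covered.** 1 − 1/1.2 = 16.7%.

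**Step 4: what remains after a 20% loss.**
- 797 × 0.8 = 637.6, so 637 children against 664 required (27 short).
- 436 × 0.8 = 348.8, so 348 against 363 (15 short).
- 76 × 0.8 = 60.8, so 60 against 63 (3 short).

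**Step 5: margins with those numbers.** e = z·√(0.25/n)·√((N − n)/(N − 1)).
- Total: 2.576 × 0.5/√637, correction practically 1: 5.10%.
- Accelerometry: 2.576 × 0.5/√348 × √(449/796) = 6.90% × 0.751 = 5.19%.
- MRI: 1.645 × 0.5/√60 × √(737/796) = 10.62% × 0.962 = 10.22%.

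**Step 6: totals that would keep both 20% and the original margins.**
- Total: 664/0.8 = 830.
- Accelerometry with N = 830: 663.49/(1 + 662.49/830) = 368.98, so 369; 369/0.8 = 461.25, so 462. The 454 in the table keeps N = 797 and does not belong with a total of 830.
- MRI with N = 830: 67.64/(1 + 66.64/830) = 62.6, so 63; 63/0.8 = 78.75, so 79.

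**The case against.** The strongest objection is that little depends on this. The margins move by 0.1 to 0.2 percentage points, and they describe the estimation of a 50% proportion, whereas the data analysis plan for the cross-sectional study is about associations, using general linear, multilevel and mediation models. No analysis described there uses these margins. That stands, and it is why the point is minor. It does not make the stated dropout allowance correct.

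It can also be said that the article never gives its inflation formula. True, but three separate figures match exactly under one rule and none matches under the other.

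A reader might go further and infer that the cross-over size of 32 has the same error, since there too "A loss rate of 20% was considered", and that its power falls below the stated 80%. The document does not support this:
- The stated difference of 71.50 ms and SDs of 93.1 and 91.6 (pooled 92.35) give, for 80% power and two-sided 5%, 26.19 per group by the normal formula.
- 26.19 × 1.2 = 31.4, which rounds up to 32, but only without the prior rounding-up that the other three figures need. With it, 27 × 1.2 = 32.4, which rounds up to 33. Division gives 26.19/0.8 = 32.7. So 32 does not reveal the rule.
- With 25 left, power would be 76.5% (t) or 78.1% (normal) if the test is two-sided and the groups independent. The article states no sidedness; one-sided, power is 85.4%. Each boy takes all three conditions, and in a paired comparison 25 boys pass 80% once the within-subject correlation exceeds about 0.12 (an assumption, as the article gives no correlation).

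**Conclusion.** The point holds for the three precision-based sizes. The totals of 797, 436 and 76 cover a loss of 16.7%, and under the stated 20% they deliver margins of about 5.1%, 5.2% and 10.2% in place of 5%, 5% and 10%. This rests on the standard proportion formula with finite-population correction, which the article does not name but which reproduces all three figures, and on reading dropout as a share of those enrolled. Severity is minor: it is a wrong statement about what the numbers allow for, with little practical effect. The cross-over size is outside the claim.

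**What to change.** Change the text in the two cross-sectional sample-size sections in one of two ways:
- keep 797, 436 and 76 and state that they allow for a 16.7% loss; or
- keep the 20% and state that the margins of error after that loss are about 5.1%, 5.2% and 10.2%.

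Either costs only wording. If the sponsor prefers to keep both the 20% and the original margins, the sizes are 830 in total, 462 for accelerometry and 79 for MRI, with the subsamples recalculated from 830. That means enrolling 33 more children, with 26 more accelerometer recordings and 3 more scans, which the small gain in precision hardly requires. In each case, one clause saying how the dropout was applied would make the figures checkable.

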##### Subsample

Due to limitation of materials and economic resources, accelerometer recordings and MRI will be assessed in two subsamples. Regarding the accelerometry (ACC) subsample, children will be selected considering the percentage of participation from each school. In the case of the MRI subsample, equal participation of boys and girls will be guaranteed. Children will be included in the randomization if they i) have all previous measurements validated, ii) do not present any visual impairment, so they can correctly perceive the visual stimuli be presented for the functional imaging, iii) have no physical or neurological problem, and iv) are right-handed children, as previous research indicates that brain measures might be different between left- and right-handed people [54]. For the cross-over design, inclusion criteria will be: i) boys aged 12–13 year-old, ii) to have a score > 2 points in Tanner pubertal timing scale [55] iii) normal vision, iv) not being part of the government’s educational integration program (i.e. psychological problems, attention deficit/hyperactivity disorder, depression), v) not having any physical problem that is incompatible with intense PA, vi) not being under psychoactive medications, and vii) to have approved guardians and children’s informed consent.

##### Subsample size and power

From those 797 children, for the calculation of the ACC subsample, we assume an alpha error of 5%, a confidence interval of 99, 50% of heterogeneity, and a 20% dropout, resulting in 436 participants. For the MRI subsample calculation an error of 10% was assumed, with a confidence interval of 90, 50% of heterogeneity, and with a 20% dropout, resulting in 76 participants.

#### Cross-over study

##### Total sample

Inclusion/exclusion criteria will be, boys from 7th to 8th grades (12–13 years old) who not present any physical, psychiatric and/or psychological disability and that they have received the approval of their parents.

##### Total sample size and power

For feasibility reasons, the school chosen for the development of exercise sessions is close to our laboratory. Sample size is estimated according to the mean difference of two independent samples from a randomized controlled trial were a working memory task (2-back) was tested [56]. Children control group achieved a positive variation (∆ = 2.05 ms; SD = 93.1) while exercise group a negative variation (∆ = − 69.45 ms; SD = 91.6) [56]. A loss rate of 20% was considered. Statistical power analysis indicated that at least 32 participants would yield adequate power (i.e., > 80%) and α (i.e., < 0.05), with a detectable variation of 71.50 ms (∆ between experimental conditions – control condition).

